## Abstract

**Background:**

Ischemic heart disease and degenerative encephalopathy are two main sources of disease burden for the global elderly population. Coronary heart disease (CHD) and cognitive impairment, as representative diseases, are prevalent and serious illnesses in the elderly. According to recent research, patients with CHD are more likely to experience cognitive impairment and their cognitive ability declines more quickly. Vascular risk factors have been associated with differences in cognitive performance in epidemiological studies, but evidence in patients with CHD is more limited. Inextricably linked between the heart and the brain. Considering the unique characteristics of recurrent cognitive impairment in patients with CHD, we will further study the related risk factors. We tried to investigate the potential predictors of cognitive impairment in patients with CHD through a prospective, cross-sectional study.

**Methods:**

The cross-sectional study design will recruit 378 patients with CHD (≥65 years) from Xiyuan Hospital of China Academy of Chinese Medical Sciences. The subjects' cognitive function is evaluated with MoCA scale, and they are divided into cognitive impairment group and normal cognitive function group according to the score results. Demographic data, disease characteristics (results of coronary CT/ angiography, number of stents implanted, status of diseased vessels), laboratory tests (biochemistry, coagulation, serum iron levels, pulse wave velocity), metabolites (blood samples and intestinal metabolites), and lifestyle (smoking, alcohol consumption, sleep, physical activity) will be assessed as outcome indicators. Compare the two groups and the correlation analysis will be performed on the development of mild cognitive impairment. Mann-Whitney U or X^2^ test was selected to describe and evaluate the variation, and logistics regression analysis was employed to fit the prediction model. After that, do the calibration curve and decision curve to evaluate the model. The prediction model will be validated by a validation set.

**Discussion:**

To explore the risk factors related to mild cognitive impairment (MCI) in patients with CHD, a new predictive model is established, which can achieve advanced intervention in the occurrence of MCI after CHD. Owing to its cross-sectional study design, the study has some limitations, but it will be further studied by increasing the observation period, adding follow-up data collection or prospective cohort study. The study has been registered with the China Clinical Trials Registry (ChiCTR2200063255) to conduct clinical trials.

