## 2. Methods and analysis

### 2.1. Study design and participants

This is a prospective, cross-sectional study with 378 participants. After screening according to the inclusion and exclusion criteria, the informed consent of the subjects was obtained. According to whether CHD patients are accompanied by mild cognitive impairment, the researchers will divide them into a cognitive impairment group (observation group) and a normal cognitive function group (control group). It is based on the program “Research on the Transformation and Application of TCM in the Prevention and Treatment of Secondary Cognitive Impairment of Coronary Heart Disease” sponsored by the Chinese Academy of Chinese Medical Sciences (CI2021A01406) to identify the risk factors for cognitive impairment in CHD patients. The fieldwork for this study will be conducted at Xiyuan Hospital of China Academy of Chinese Medical Sciences in China. Both outpatients and inpatients are allowed to be included. Depending on the feasibility and specific implementation, additional hospital sites may be added. In addition, this study has been registered as a clinical trial by the Chinese Clinical Trials Registry (ChiCTR2200063255), which further standardizes our research. The specific overview of study procedure is shown in Figure 1.

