#### 2.4.2. Cognitive assessment

At baseline, all participants underwent cognitive assessment. Global cognitive function will be assessed using the MoCA scale. Neuropsychological scale screening tests are crucial in the identification of cognitive impairment. Currently, the Mini-Mental State Examination (MMSE) and Montreal Cognitive Assessment (MoCA) are the most commonly used cognitive assessment tools. Of the two, MoCA covers a wider variety of cognitive domains than MMSE. In addition, meta-analysis findings (18) revealed that the sensitivity, specificity and AUC value of MoCA are higher than those of MMSE in elderly patients (over 60 years old) with MCI. Therefore, we choose MoCA as the screening method to determine whether there is MCI.

As a screening tool specially developed to detect MCI, it takes around 10 min to administer MoCA when executed (19). The MoCA covers 14 topics with a total of 30 points, including visual spatial structure skills, executive function, attention and concentration, short-term memory and delayed recall, language, abstract thinking, calculation and orientation. Due to varied geographies, cultures and populations, there are some differences in the cut-off values of MoCA screening for MCI among elderly individuals in various regions. Studies have shown that when using a cutpoint of 25/26, the MoCA has a sensitivity of 80–100% and specificity of 50 to 76% for detecting MCI (20). According to a survey to evaluate MCI in Beijing, China's urban and rural old communities, MoCA has excellent sensitivity and fairness specificity under the recommended critical score of 26 (21). The systematic review of MCI screening for the elderly in China also concurs that using a diagnostic threshold of 25/26 is the most practical option (22). Thus, the score of MoCA <26 is chosen as the benchmark to ascertain whether MCI exists in this study.

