#### 2.4.4. Laboratory indicators

Laboratory examination can accept the test results within 7 days before and after screening. It mainly includes the following contents: fasting glucose, glycosylated hemoglobin (HbA1c), total cholesterol, triglyceride, low-density lipoprotein, high-density lipoprotein, total bilirubin, serum creatinine, serum iron level (Fe), coagulation function (PT, APTT, TT, FIB), vascular ultrasound pulse wave velocity (PWV).

In addition to the above-mentioned indexes, in the early morning of the 2nd day after the selection, two tubes of peripheral venous blood of 5 ml will be drawn from a qualified phlebotomist and placed in the EDTA anticoagulant tubes. Centrifuge the blood samples (3,000 rpm at 4°C for 15 min), store them at −80°C, and then conduct untargeted metabolomics detection. 2 g of fresh fecal samples will be collected and put into aseptic collection tube and stored at −80°C immediately for metabolic detection and analysis of intestinal flora.

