## 3. Discussion

Age-related cognitive decline is a series of natural cognitive changes that may develop into MCI or dementia. MCI is a state of cognitive impairment between healthy aging and dementia, which is considered as the prophase of dementia (25). But at this stage, the function of daily life remains basically intact. Delaying the onset of cognitive decline is the optimal strategy but where there are some earlier measures to slow the decline is important. Through comparative analysis of the population characteristics of the two groups, our study will screen out the specific markers of cognitive impairment in patients with CHD. So as to provide reference for early clinical identification and intervention of the disease.

The objective of this study is to ascertain the relationship between CHD and its risk factors and cognitive impairment in the elderly. At the same time, establish the risk prediction model of cognitive impairment in patients with CHD. The study will make available data regards CHD and MCI risk prediction. We propose leveraging the progress of machine learning to systematically compare different modeling approaches (26) to develop predictive tools for cognitive impairment in patients with CHD and verify their effectiveness. Comprehensive application of clinical observation, multi-source data processing, machine learning and other methods is also the innovation of the study.

Still, this research is subject to certain limitations. As an observational study, cross-sectional design has limitations e.g., causality cannot be inferred, we can only address the association. However, we try to include more observation factors, which are widely related to basic demographic data, disease characteristics, blood chemistry, metabolites and lifestyle. It is expected that some risk factors with clinical value can be found on the basis of this exploratory analysis. In order to broaden the current knowledge on CHD and its relationship with cognitive impairment in the elderly. Additionally, it will serve as a valuable foundation for hypothesis generation for future longitudinal studies and / or randomized controlled trials. In the future, it is necessary to conduct a larger sample of prospective cohort studies and add follow-up time to determine the incidence of secondary MCI in patients with CHD.

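### The Abstract credits the model with enabling action before MCI occurs, but a study at one time point can only model who has MCI now

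*Protocol article*

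**What the plan says.** Two places in the Abstract describe the work in terms of MCI arising over time. The Discussion part says that "a new predictive model is established, which can achieve advanced intervention in the occurrence of MCI after CHD". The Methods part says that "the correlation analysis will be performed on the development of mild cognitive impairment". More loosely, section 3 adds: "The study will make available data regards CHD and MCI risk prediction".

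The design is stated in section 2.1: "This is a prospective, cross-sectional study with 378 participants". On the outcome, section 2.4.2 says "At baseline, all participants underwent cognitive assessment", and the Abstract's Methods part says of the subjects that "they are divided into cognitive impairment group and normal cognitive function group according to the score results". On the timing of predictors, section 2.4.4 says "Laboratory examination can accept the test results within 7 days before and after screening", and blood for metabolomics is drawn "in the early morning of the 2nd day after the selection".

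Section 2.6 compares the two existing groups and fits a logistic model to group membership. No later cognitive assessment is described. Follow-up appears only as further work, in the Abstract and at the end of section 3.

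**The concern.** A model of occurrence needs people who are free of MCI at a defined start, predictors measured at that start, and a later assessment that shows who has developed MCI. This study has one assessment. Its cases are prevalent: they have had MCI for an unknown time when their predictors are recorded.

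Two things are at stake. The first is what the model's output means: a fitted probability of 0.40 would mean a 40% chance of having MCI at the assessment, with no time horizon attached. The second is how its performance is read. The AUC, bootstrap check, calibration curve, decision curve and validation set would, as far as the article shows, all score the model against MCI status at the same time point. Good results would support detection, yet beside the Abstract's sentence they would seem to support forecasting.

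**Working it through.** The claim carries no figure, so the check sets the stated design against what the claim requires.

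**Step 1. Timing of outcome and predictors.**

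| Element | Where stated | Timing |
|---|---|---|
| MCI status | Abstract (Methods), 2.4.2 | once, at baseline |
| Routine laboratory tests and pulse wave velocity | 2.4.4 | within 7 days either side of screening |
| Blood for metabolomics | 2.4.4 | shortly after selection |
| Sleep (PSQI) and activity (IPAQ-S) | 2.4.3 | no repeat described |
| Later cognitive assessment | none described | – |

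Collection may spread over some days, but it amounts to one time point. Laboratory values may even postdate the cognitive assessment.

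**Step 2. What the model estimates.** With Y = MCI at baseline and X = the predictors, the analysis in 2.6 estimates P(Y = 1 given X). The claim needs P(MCI by a later time, given X and no MCI at baseline). Nobody in the normal-cognition group is re-assessed, so the data hold no information on the second quantity.

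**Step 3. Does sample size matter?** The stated total reproduces: 18 factors × 10 = 180; 180 × 1.05 = 189; 189 × 2 groups = 378. The doubling is inferred, since section 2.3 does not write it out. To give a scale, assume that the 42.4% cited in 2.3, which comes from a follow-up study, applies as a prevalence here:

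- prevalent cases: 378 × 0.424 ≈ 160
- over the 35–46% range in section 1: 378 × 0.35 ≈ 132 to 378 × 0.46 ≈ 174
- incident cases observed by design: 0

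A larger sample raises the first two lines and leaves the last at 0.

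**Step 4. Order of events.** Table 1 requires CHD for at least 3 years and excludes cognitive impairment or dementia diagnosed before CHD was. Undiagnosed impairment that predates CHD is not excluded, so even the order MCI after CHD is only partly secured. Among the predictors, education, family history and number of stents are fixed or look back in time. Sleep, physical activity, metabolites and current drugs may follow from MCI rather than precede it.

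**Step 5. Consistency within the article.** Section 3 says that the design supports statements of association but not of causation, and that a larger cohort with follow-up is needed to establish how often MCI arises in patients with CHD. The Abstract claims use of a model for an event whose incidence section 3 says remains to be determined.

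**The case against.** The strongest reply is that the article already concedes most of this. The sentence directly after the claim admits limitations of the cross-sectional design and points to follow-up or a cohort. Section 3 limits the work to association, calls it exploratory and presents it as a basis for hypotheses. Section 1 states a milder aim, a reference for early recognition and intervention, and section 3 repeats it. Prediction can properly include diagnostic prediction.

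Much of that stands. The aim in section 1 fits a case-finding model and needs no change, and the reference to risk prediction in section 3 is general wording that gives little support to the criticism by itself. But the disclosures do not withdraw the Abstract's sentence. Causality is also a different matter: a non-causal model can forecast well if it is built on follow-up data, which this one is not. Acting ahead of the occurrence of MCI has no diagnostic reading.

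A reader might infer three stronger criticisms that the document does not support:

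- **That the score is specified for use in cognitively normal patients.** No section says so or gives a forecast horizon. Such use would follow from taking the Abstract literally, but it is not described.
- **That odds ratios will be reported as risk multipliers.** Section 2.6 promises odds ratios with confidence intervals and no more. Odds ratios overstate ratios of proportions for any common outcome, in a cohort as well, so this is not a consequence of the cross-sectional design.
- **That the term risk factor must be replaced throughout.** This is largely terminology, given the stated limit to association.

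**Conclusion.** The point holds, confined to the claim about occurrence and development. The article attributes to its model a property that the design cannot give it, and its own section 3 says otherwise. The study can yield a model for detecting current MCI; performance in forecasting new MCI cannot be estimated from its data at all. The possibility that some predictors result from MCI applies to a subset and adds to the case, which does not depend on it.

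The conclusion assumes that no later cognitive assessment belongs to this study; the article describes none and places follow-up in future work. It does not depend on the assumed prevalence, the sample size or the significance level. The correction should be made, because it changes what the study may conclude, but it does not call the data collection or the planned regression into question.

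**What to change.** 1. State the deliverable in the Abstract and section 3 as a case-finding (diagnostic) model for the probability of current MCI in patients aged 65 or over with CHD for at least 3 years. This agrees with the aim already given in section 1.
2. In the Abstract, remove the wording on intervening ahead of the occurrence of MCI (Discussion part) and on its development (Methods part).
3. In section 2.6 or section 3, say that the AUC, calibration, decision-curve and validation results describe detection of current MCI only.
4. Extend the limitations in section 3 beyond causality: no follow-up, prevalent cases of unknown onset, some predictors that may follow MCI, and exclusion only of impairment already diagnosed before CHD.
5. Leave forecasting to the future cohort, with participants free of MCI at its start and re-assessed later.

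The cost is a few sentences and a more modest claim. Eligibility, measurements, the total of 378 and the analysis steps stay as they are.

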## 1. Introduction

With the deepening of population aging, the incidence of cardiovascular and cerebrovascular diseases is increasing annually, which brings heavy social and economic burden. Coronary heart disease (CHD) and cognitive impairment are major diseases that endanger human health, especially for the elderly. Cognitive impairment includes varying degrees from mild cognitive impairment (MCI) to dementia. When memory or other cognitive functions are impaired but not to the point of dementia, this is referred to as MCI (1). Epidemiological investigation have shown that 10–15% of MCI patients develop dementia each year among people over 65 years old (2), while about 70 % of Alzheimer's disease (AD) patients in China are evolved from MCI (3). Hence, it has significant clinical value for the early recognition, early diagnosis and transformation prediction of the disease.

Studies have shown that those with CHD are more likely to experience cognitive impairment. Compared to the general population, the prevalence rate is much greater at roughly 35–46% (4–6). A clinical study published in The New England Journal found that the incidence of cognitive decline in patients with CHD was 42% five years after coronary-artery bypass grafting (CABG) (6). A significant longitudinal cohort research with 7,888 participants (mean age 62.1 ± 10.2 years) indicated that CHD incidents were linked to accelerated cognitive decline. The decline in cognitive ability (including overall cognitive, verbal memory, and time orientation scores) occurred in the years after the diagnosis CHD (7). Similar findings were made by other researchers who discovered that after a follow-up of 3.2 ± 0.37 years, patients with stable CHD had a 42.4% incidence of cognitive impairment (4). In view of this, our study intends to focus on elderly patients with a history of coronary heart disease over 3 years, because of the high incidence of MCI at this stage. Additionally, cardiovascular disease risk factors such as hyperlipidemia, hypertension, diabetes, obesity, smoking and so on are also risk factors of cognitive impairment (8, 9). Clinical observation revealed that cognitive impairment was more pronounced in patients with significant three-vessel disease or coronary artery stenosis (10). Researchers discovered that people with a history of myocardial infarction had a 2–5 times higher chance of developing dementia (7).

The impact of cardiovascular event chain (from cardiovascular risk factors to end-stage heart diseases) characterized by coronary atherosclerosis has expanded to organs outside the heart, particularly the brain, and affects cognitive performance (11, 12). It is of great significance to further study the relationship between CHD and cognitive impairment. Therefore, our study soughts to assess the correlation between CHD and MCI in the elderly by examining the differences of coronary heart disease and its risk factors between patients with cognitive impairment and patients with normal cognition. At the same time, a risk prediction model will be established to provide reference for early clinical identification and intervention of cognitive impairment in patients with CHD. In order to achieve the objective of preventing risk factors from occurring and enhancing cognitive performance.

## 2. Methods and analysis

### 2.1. Study design and participants

This is a prospective, cross-sectional study with 378 participants. After screening according to the inclusion and exclusion criteria, the informed consent of the subjects was obtained. According to whether CHD patients are accompanied by mild cognitive impairment, the researchers will divide them into a cognitive impairment group (observation group) and a normal cognitive function group (control group). It is based on the program “Research on the Transformation and Application of TCM in the Prevention and Treatment of Secondary Cognitive Impairment of Coronary Heart Disease” sponsored by the Chinese Academy of Chinese Medical Sciences (CI2021A01406) to identify the risk factors for cognitive impairment in CHD patients. The fieldwork for this study will be conducted at Xiyuan Hospital of China Academy of Chinese Medical Sciences in China. Both outpatients and inpatients are allowed to be included. Depending on the feasibility and specific implementation, additional hospital sites may be added. In addition, this study has been registered as a clinical trial by the Chinese Clinical Trials Registry (ChiCTR2200063255), which further standardizes our research. The specific overview of study procedure is shown in Figure 1.

**Figure 1 F1:**
[figure not shown]
Flow chart of specific steps.

### 2.2. Recruitment and screening

Eligible patients were identified according to the diagnostic description and the International Classification of Diseases (10th and 11th editions). The recruitment of subjects was carried out through offline and online announcements, focusing on offline treatment process. Eligible patients are expected to be enrolled between September 2022 and December 2023. The diagnostic criteria of CHD refer to “guidelines for diagnosis and treatment of stable coronary heart disease” (13) and “guidelines for emergency rapid diagnosis and treatment of acute coronary syndrome (2019)” (14).

For the diagnostic criteria of MCI, refer to the Chinese guidelines on mild cognitive impairment (15). Specifically: (i) cognitive impairment was reported by patients or insiders, or experienced clinicians found cognitive impairment; (ii) objective evidence of impairment of one or more cognitive domains (from cognitive tests); (iii) sophisticated instrumental daily abilities might be slightly hampered, but still preserve independent daily living abilities; iv unable to reach the diagnosis of dementia. Auxiliary diagnostic criteria: the score of Montreal Cognitive Assessment (MoCA) scale <26 points; the score of Clinical Dementia Rating (CDR) scale was 0 or 0.5. MoCA: the full score of the scale is 30, and the score ≥26 is normal. If the subjects' years of education are <12 years (senior high school level), the results can be increased by one point.

All the above are diagnosed by the attending physician. Under the premise of full informed consent, it will be screened by the researcher or the attending physicians according to the requirements. The inclusion and exclusion criteria for this study are shown in Table 1.

**Table 1 T1:** Inclusion criteria and exclusion criteria of the study.

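### The attending physician makes the MCI diagnosis partly on clinical impression and would ordinarily know coronary severity, which is a tested predictor; the grouping rule, MoCA rater and order of assessments should be fixed

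*Protocol article*

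**What the plan says.** **Who diagnoses.** Section 2.2 gives the CHD criteria, then the MCI criteria, then states "All the above are diagnosed by the attending physician". Screening is less specific: "it will be screened by the researcher or the attending physicians according to the requirements".

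**On what basis.** The first MCI criterion is met if "cognitive impairment was reported by patients or insiders, or experienced clinicians found cognitive impairment". In that section the MoCA cut-off is an auxiliary criterion. The one-point education correction is worded as something that may be added, not as something that is always added.

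**How groups are formed.** The Abstract (Methods) says "they are divided into cognitive impairment group and normal cognitive function group according to the score results". Section 2.4.2 says "the score of MoCA <26 is chosen as the benchmark to ascertain whether MCI exists in this study". Section 2.1 says "the researchers will divide them into a cognitive impairment group (observation group) and a normal cognitive function group (control group", depending on whether MCI is present.

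**Predictors.** Section 2.4.1 lists coronary CT or angiography results, stents, diseased vessels, cardiac function class and past diseases. Section 2.4.3 adds the PSQI and IPAQ-S. On timing, section 2.4.4 says "Laboratory examination can accept the test results within 7 days before and after screening", and it places the metabolomics blood draw on the second day after selection.

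**Safeguard.** Section 2.5 describes training, including in MoCA collection, and uniform judgement standards. Masking is not mentioned.

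**The concern.** The study's product is a set of associations between predictors and MCI group, and a prediction model built from them. Those associations are credible only if the outcome is rated without regard to the predictors, and the predictors are recorded without regard to the outcome.

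The first condition is at risk through an assignment that the article states. The physician who treats the coronary disease also judges whether MCI is present. The Introduction reports that impairment is more pronounced with three-vessel disease or coronary stenosis, and that dementia is 2 to 5 times more likely after infarction. Section 2.5 requires every investigator to know the protocol thoroughly. A rater who expects impairment in severe patients may find it more readily, or may withhold the optional education point, and a score near 26 then changes group.

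The second condition is less certain. It concerns only the self-report and history items, where probing could differ if the MoCA result is known.

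The analysis would not reveal either problem. Section 2.6 admits covariates at P<0.1 to forward stepwise selection, so a modest spurious association can enter the model. Bootstrap validation resamples the same labels and cannot detect that they are biased.

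**Working it through.** **1. The plan's own figure.** The article gives no number on this point. Its one design figure reproduces: 18 factors × 10 = 180; × 2 groups = 360; × 1.05 = 378. The doubling is inferred, because section 2.3 does not show that step. The point does not depend on 378, which is used below only for an even split of 189 and 189.

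**2. The two grouping rules side by side.**

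| Place | What decides the group | Room for judgement |
|---|---|---|
| Section 2.2 | Physician's diagnosis; MoCA auxiliary | Clinician's impression; optional education point |
| Abstract and section 2.4.2 | MoCA below 26 | Item scoring; optional education point |

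The rules are not interchangeable. Section 2.4.2 quotes a specificity of 50–76% at this cut-off, so 24–50% of patients without MCI would score below 26. The article does not say which rule prevails when they disagree.

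**3. Which predictors are exposed.**
- Laboratory results may date from up to 7 days before screening and are instrument readings.
- Coronary imaging, stents and disease course are largely history.
- The metabolomics sample is drawn after selection, but the assay is objective.
- The PSQI, IPAQ-S and history questionnaire have no stated order relative to the MoCA.

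**4. Illustration A: a shift in MoCA scoring.** Assumptions not in the documents: MoCA is normal with SD 3 or 4, and 42.4% of patients with milder coronary disease score below 26. The 42.4% is the rate cited in section 2.3 and is borrowed here. Scores are whole numbers, so the cut is placed at 25.5. Since Φ⁻¹(0.424) ≈ −0.192, the case rate after a downward shift d in severe patients is Φ(−0.192 + d/SD). The OR is its odds divided by 0.424/0.576 = 0.736.

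| d (points) | Rate, SD 4 | OR, SD 4 | Rate, SD 3 | OR, SD 3 |
|---|---|---|---|---|
| 0.25 | 0.449 | 1.11 | 0.457 | 1.14 |
| 0.5 | 0.473 | 1.22 | 0.490 | 1.31 |
| 1.0 | 0.523 | 1.49 | 0.556 | 1.70 |

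The optional education point alone cannot create an average difference above 1 point, and would reach that only if applied wholly one-sidedly to patients who all qualify for it.

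**5. Illustration B: a shift in classification.** Take a binary predictor unrelated to MCI (true OR 1), true MCI 42.4%, sensitivity 80%, and specificity 76% or 50% (values from section 2.4.2). Suppose that knowing the predictor raises sensitivity and lowers specificity by the same amount (assumed).
- By 5 points, specificity 76%: exposed 0.424 × 0.85 + 0.576 × 0.29 = 0.527; unexposed 0.424 × 0.80 + 0.576 × 0.24 = 0.477; OR 1.22.
- By 5 points, specificity 50%: 0.677 against 0.627; OR 1.25.
- By 10 points: 0.577 against 0.477, OR 1.50; and 0.727 against 0.627, OR 1.58. With 189 per side, the chance of p<0.05 is about 50% and 55%.

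**The case against.** The strongest reply is that a scored scale with a fixed cut-off decides the group, and that section 2.5 has researchers trained in MoCA collection. A trained researcher may therefore already do the rating. This stands in part. It limits discretion but does not remove it: section 2.2 still gives the MCI diagnosis to the attending physician, and the education point is optional.

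A second reply is that a condensed article may leave masking, form order and sample labelling to the full protocol. This also stands. Silence does not show that masking is absent, and sample labelling is not pressed here. The physician's role is different, because the article states it.

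Three stronger readings are tempting and are not supported:
- *That predictors are collected with the group already known.* No sentence says so. Laboratory results may precede screening, selection may mean enrolment and not grouping, and the flow chart of steps was not available.
- *That knowing a patient has CHD biases the rating.* Every participant has CHD of at least 3 years, so CHD status cannot differ between groups. Only knowledge of severity or comorbidity can.
- *That most predictors are affected.* Age, laboratory values, metabolites and stent counts are hard to bias. The article does not even state whether the PSQI and IPAQ-S are taken by interview.

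**Conclusion.** The point holds in a limited form. By stated assignment, a physician who would ordinarily know coronary severity makes the MCI diagnosis, partly on impression, while two other places in the article group by MoCA score. Collection of the PSQI, IPAQ-S and history items with the MoCA result known is possible but not shown. A reader might infer that outcome and predictors are in fact rated dependently; the documents show a risk, not an occurrence.

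The size is unknown. Odds ratios of 1.1 to 1.7 follow from assumed shifts of 0.25 to 1 point and an assumed SD of 3 to 4, and 1.22 to 1.58 from assumed 5- to 10-point changes in accuracy. They show that small rating differences could matter, and they are not estimates of bias in this study. What remains assumed is that the attending physician knows the coronary findings when judging cognition. This is a cheap improvement and not a fatal flaw.

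**What to change.** 1. **Grouping rule.** Reconcile section 2.2 with the Abstract and section 2.4.2 so that, for study grouping, the MoCA score alone assigns the group. Make the education correction automatic: the same rule for every patient who meets the stated education limit.
2. **Rater.** Have a researcher already trained under section 2.5, and not the treating physician, administer the MoCA without the coronary report, and lock the score.
3. **Order.** Complete the PSQI, IPAQ-S and history questionnaire before the MoCA.
4. **Patients already enrolled.** The ethics statement says recruitment is under way. Flag those rated before the change and repeat the main model without them as a sensitivity analysis.

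The cost is a procedural paragraph and a page order on the case report form. No new staff are needed. The downside is some rotation of tasks at the single site. If these arrangements already exist in the full protocol, a sentence in section 2.2 saying so, together with the reconciled grouping rule, would settle the point.
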